## Abstract

**Background:**

Fabry disease (FD) is a genetic disorder caused by a deficiency in the enzyme alpha-galactosidase A, leading to an accumulation of glycosphingolipids in tissues across the body. Cardiac disease is the leading cause of morbidity and mortality. Advanced disease, characterised by extensive left ventricular hypertrophy, ventricular dysfunction and fibrosis, is known to be associated with an increase in arrhythmia. Data identifying risk factors for arrhythmia are limited, and no Fabry-specific risk stratification tool is available to select those who may benefit from initiation of medical or device therapy (implantable cardiac defibrillators). Current monitoring strategies have a limited diagnostic yield, and implantable loop recorders (ILRs) have the potential to change treatment and clinical outcomes.

**Aim:**

The aim of this study is to determine whether ILRs can (1) improve arrhythmia detection in FD and (2) identify risk predictors of arrhythmia.

**Methods:**

A prospective, 5-year, open-label, international, multi-centre randomised controlled trial of a minimum of 164 participants with genetically or enzymatically confirmed FD (or both) who have evidence of cardiac disease will be recruited from five centres: Queen Elizabeth Hospital, Birmingham, UK; Salford Royal Hospital, Salford, UK; Royal Free Hospital, London, UK; Addenbrookes Hospital, Cambridge, UK; and Westmead Hospital, Sydney, Australia. Participants will be block-randomised (1:1) to two study arms for cardiac monitoring (i) control arm: standard of care with annual 24 h or 5-day Holter monitor or (ii) treatment arm: continuous cardiac monitoring with ILR implantation plus standard of care. Participants will undergo multiple investigations—blood/urine biomarkers, 12-lead and advanced electrocardiogram (ECG) recording, echocardiography and cardiovascular magnetic resonance (CMR) imaging—at baseline and 6–12 monthly follow-up visits. The primary endpoint is identification of arrhythmia requiring initiation or alteration in therapy. Secondary outcome measures include characterising the risk factors associated with arrhythmia and outcome data in the form of imaging, ECG and blood biomarkers.

**Discussion:**

This is the first study evaluating arrhythmia burden and the use of ILR across the spectrum of risk profiles in Fabry cardiomyopathy. This will enable detailed characterisation of arrhythmic risk predictors in FD and ultimately support formulation of Fabry-specific guidance in this high-risk population.

**Trial registration:**

ClinicalTrials.gov (NCT03305250). Registered on 9 October 2017.

**Electronic supplementary material:**

The online version of this article (10.1186/s13063-019-3425-1) contains supplementary material, which is available to authorized users.

## Background

Fabry disease (FD) is an X-linked lysosomal storage disorder in which a deficiency in the enzyme alpha-galactosidase A [1] leads to a progressive accumulation of glycosphingolipids such as globotriaosylceramide (Gb3) and globotriaosylsphingosine (lyso-Gb3) in tissues across the body [2]. Cellular changes within the tissue microenvironment lead to extensive cardiovascular, neurological and renal dysfunction. Clinical presentation can be extremely variable [3] and developments in therapy have changed the natural progression of FD, such that cardiac disease has surpassed renal involvement as the leading cause of morbidity and mortality [4]. Cardiovascular involvement is characterised by progressive glycosphingolipid storage, inflammation, left ventricular hypertrophy (LVH), fibrosis, arrhythmia, congestive cardiac failure and sudden death [5]. Although a significant proportion of cardiovascular deaths are ascribed to ‘sudden cardiac events’ and symptoms such as palpitations and syncope are almost universal, very little is known regarding the true frequency of arrhythmia. Registry data have suggested that the rate of atrial arrhythmia could be as high as 13% [6]. However, the incidence of ventricular arrhythmia varies widely (5% to 30%) [6]. Advanced cardiac disease characterised by extensive LVH, ventricular dysfunction and fibrosis is known to be associated with an increase in arrhythmia needing intervention. This includes bradyarrhythmia requiring a permanent pacemaker (PPM), ventricular arrhythmia requiring an implantable cardiac defibrillator (ICD) and atrial fibrillation (AF) requiring anticoagulation [7]. Limited data have identified LVH, the presence of late gadolinium enhancement (LGE) left atrial (LA) dilatation, a QRS duration of more than 120 ms and an elevated Mainz Severity Score Index (MSSI) as potential arrhythmic risk factors. However, there is no Fabry-specific risk calculator to select those who might benefit most from therapeutic interventions (such as ICDs) as there are for conditions such as hypertrophic cardiomyopathy (HCM) [8]. Novel electrical and blood biomarkers have also recently emerged as potential predictors of atrial and ventricular arrhythmia. Advances in technology have enabled computerised electrocardiogram (ECG) analysis using advanced signal averaging, vectorcardiographic reconstruction, singular value decomposition of QRS and T wave complexity, frequency content analysis, and beat-to-beat variability—collectively known as advanced ECG (A-ECG). These A-ECG measures can be applied retrospectively to digital files of clinically acquired ECGs, and outcome variables identified as potential arrhythmic risk markers [9–11]. These markers have a higher sensitivity and specificity than conventional ECG criteria in prediction of arrhythmic risk and assessment of conditions such as LVH and HCM [12, 13]. Cardiac involvement is a major determinant of morbidity and mortality in FD. ECG changes do not always reflect the extent of cardiac disease, making assessment with conventional ECG limited [14, 15]. Thus, detailed analysis of surface ECG markers through A-ECG could be a powerful tool not only to assess risk of arrhythmia but potentially to track cardiac pathology in FD.

Local myocardial inflammation has also been shown to alter electrophysiological properties and contribute to the arrhythmic vulnerability of cardiac tissue. Specific inflammatory biomarkers, such as interleukin-6 (IL-6) and high-sensitivity C-reactive protein (hs-CRP), have both been considered potential contributors to the pathophysiological mechanisms leading to the development of malignant ventricular arrhythmia and atrial arrhythmias, such as AF [16, 17]. Although there are no data on the role of IL-6 or hs-CRP in predicting arrhythmia in FD, the presence of scar identified by LGE on cardiovascular magnetic resonance (CMR) is known to be a risk factor and these lesions in some patients with FD have been linked to chronic inflammation [18]. As such, their evaluation may provide crucial information on the potential biochemical mechanisms underlying arrhythmia generation.

Current monitoring strategies for arrhythmia are limited to a 12-lead ECG at clinic visits, annual 24-h Holter monitoring, and response to a clinical event. However, a significant difficulty in clinical management is that, owing to the frequent nature of palpitations in patients with FD, symptomatic status loses specificity for identifying arrhythmia. Implantable loop recorders (ILRs) are small and subcutaneously inserted devices that enable continuous cardiac monitoring over the course of a 3-year period. These devices have the potential to modify care and outcomes by providing definite evidence of arrhythmia and to provide greater accuracy (due to length of recording) and earlier detection with remote/home monitoring, particularly in asymptomatic individuals. Although ILRs do not carry the same risk as other implanted devices, they are still invasive and have relatively high cost, so their use needs to be justified in the current healthcare climate.

## Methods

### Design

This is a prospective, 5-year, open-label, international, multi-centre randomised controlled trial to evaluate the role of ILR in modifying therapy for arrhythmia in FD. Adults with genetic or enzymatic confirmation of FD who have evidence of cardiac involvement will be recruited from five centres: (1) Queen Elizabeth Hospital, Birmingham, UK; (2) Salford Royal Hospital, Salford, UK; (3) Royal Free Hospital, London, UK; (4) Addenbrookes Hospital, Cambridge, UK; and (5) Westmead Hospital, Sydney, Australia. Participants will be randomly assigned to one of two study arms for cardiac monitoring: (i) standard of care using annual 24-h/5-day ECG monitoring according to local practice or (ii) continuous cardiac monitoring with ILR implantation plus standard of care. A summary of the trial design is shown in Fig. 1.

**Fig. 1 Fig1:**
[figure not shown]
Study timeline. A minimum of 164 participants will undergo baseline investigation and randomisation to standard care with annual Holter monitoring or to intervention with an implantable loop recorder device for continued electrocardiogram (ECG) monitoring. All participants will be followed up at 12 monthly intervals (centre-dependent) for the entire 36-month study period, with investigations repeated at each time-point.

### Null hypothesis

There will be no difference in the identification of clinically significant arrhythmia that requires treatment modification between patients following standard care alone compared with those following standard care with the addition of ILR monitoring.

### Study aims

This trial will compare the rate of clinically significant arrhythmia requiring intervention identified between the two surveillance modalities. This information will be correlated with cardiac investigations performed at intervals (details described below) and thus the study aims are the following:Identify the true arrhythmic burden in FD.Demonstrate the clinical benefit of ILR in modifying treatment.Provide detailed data regarding specific risk factors predisposing to arrhythmic events.

This study will identify the predictive power of both traditional (LGE, QRS duration, atrial size, and left ventricular (LV) ejection fraction) and novel (troponin, pro-brain natriuretic peptide (pro-BNP), lyso-Gb3, T1 and T2 mapping, and A-ECG analysis) biomarkers. This will provide greater clarity on the risk of sudden cardiac death (SCD) and ultimately guide the formulation of a FD-specific risk stratification tool for primary prevention.

### Participants

Participants will be recruited from Fabry clinics over a 12- to 18-month recruitment period.

Inclusion criteria:Adults older than 18 years of age with confirmed FD (genotypically with a homozygous or heterozygous Fabry-specific mutation and/or enzymatically defined by absent or reduced alpha-galactosidase A)Evidence of cardiac involvement from FD, including at least one of the following:◦ Any ECG abnormality associated with FD (Table 1)◦ Low T1 on CMR imaging (below centre-specific normal range according to sex)◦ LVH on transthoracic echocardiogram or CMR (defined as maximum wall thickness (MWT) of more than 12 mm)

**Table 1 Tab1:** Electrocardiogram (ECG) abnormalities associated with Fabry disease

ECG abnormality	
Short or prolonged PR interval (<120 ms or >200 ms)	
QRS duration > 120 ms	
T-wave inversion in at least two contiguous leads	
Prolonged QTc	

Exclusion criteria:Patients with an existing cardiac device (PPM, ICD, cardiac resynchronisation therapy (CRT) or ILR)Known dual pathology:◦ Coronary artery disease (positive non-invasive imaging, confirmed myocardial infarction, previous percutaneous or surgical revascularisation). Patients more than 40 years old with symptoms that could be from coronary artery disease will have this excluded.◦ Cardiomyopathy disease causing mutation (e.g., SCN5 and MYBPC3).

The following features have been linked to an increase in the risk of cardiac arrhythmia and SCD [7]. The study population will be enriched with these arrhythmic risk factors:LVH:◦ Elevated indexed LV mass (greater than two standard deviations above age, sex and body surface area indexed measured on steady-state free precession cine imaging CMR)◦ MWT of more than 12 mmLA dilatation on two-dimensional (2D) transthoracic echocardiography:◦ M-mode measurement of more than 40 mm or biplane volume of more than 34 mLElevated biomarkers (high-sensitivity troponin T or I above local reference value)QRS duration of more than 120 ms on standard ECGPresence of LGE on CMRMSSI of more than 20 [19].

### Randomisation

A minimum of 164 participants will be recruited and randomly assigned to either the control group receiving standard of care or the intervention group who will have continuous cardiac monitoring with an ILR plus standard of care. A block randomisation process will be performed by an independent statistician in a 1:1 ratio (Fig. 2). Allocation tables will be imported to the Research Electronic Data Capture (REDCap) web application software hosted by the National Hospital for Neurology and Neurosurgery (London). REDCap is a secure web-based electronic software used to facilitate data capture for research studies [20]. All clinical data collected will be entered directly into the REDCap case report forms. Sham devices will not be used in the control group; thus, it will not be possible to blind clinicians, investigators or patients.

**Fig. 2 Fig2:**
[figure not shown]
Block randomisation process. The high-risk features include LVH (MWT > 12 mm or elevated LVMi greater than two SD), LA dilatation (M-mode measurement > 40 mm or biplane volume > 34 mL on echo), elevated troponin (above centre specific reference ranges), prolonged QRS duration > 120 ms, presence of LGE on CMR imaging, a MSSI greater than 20. *There will be a variable number of patients from each high-risk feature group to ensure a variable risk profile within the study cohort (zero risk factors – 20 participants, one risk factor – 40 participants, two risk factors – 40 participants, three risk factors – 40 participants, four or five risk factors – 24 participants. *Abbreviations*: *CMR* cardiac magnetic resonance imaging, *ECG* electrocardiogram, *ILR* implantable loop recorder, *LA* left atrium, *LGE* late gadolinium enhancement, *LVH* left ventricular hypertrophy, *LVMi* indexed left ventricular mass, *MSSI* Mainz severity score index; *MWT* maximum wall thickness, *SD* standard deviation, *TTE* transthoracic echocardiography.

### Assessment and follow-up

Following screening assessment for eligibility, all patients will undergo study entry investigations at their baseline visit. Subsequent follow-up will occur for 3 years at 6–12 monthly intervals, although recruiting centres have the option to review patients more frequently depending on clinical need. All study procedures will be repeated at follow-up visits. Figure 3 summarises the follow-up period and clinical procedures that will be undertaken at each time point. The investigations listed below will be carried out on the whole study population:Blood and urine analysis

**Fig. 3 Fig3:**
[figure not shown]
Summary demonstrating participant activity for the duration of the study. All study visits will occur during routine clinical follow-up visits for Fabry disease surveillance, with only two extra hospital visits for screening and implantable loop recorder (ILR) insertion. The shaded columns represent optional monitoring visits that will be centre-dependent. Adapted from SPIRIT (Standard Protocol Items Recommendations for Interventional Trials) figure (2013). *Abbreviations*: *CMR* cardiac magnetic resonance, *ECG* electrocardiogram, *QOL* quality of life.

Routine biochemical and haematological parameters, including plasma lipids, thyroid function, vitamin D level, high-sensitivity troponin T or I (site-dependent) and N-terminal pro brain natriuretic peptide (NT-proBNP), will be analysed. Additional biomarker analysis will include hs-CRP and IL-6. Urine samples will be collected for analysis of albumin-creatinine ratio.2.Echocardiography

A detailed transthoracic echocardiogram will be performed at each centre by an accredited echocardiographer in accordance with the British Society of Echocardiography Minimum Dataset for a Standard Transthoracic Echocardiogram [21]. Analysis will be performed locally at each centre, and ventricular dimensions, wall thickness, chamber volumes and cardiac output will be evaluated by using standard guidance [21, 22]. Left ventricular diastolic function will be evaluated at rest by using standard guidance. This will include measurement of peak early diastolic (e′) mitral annular velocities at the septal and lateral walls by using pulsed wave tissue Doppler in end-expiration, mitral valve inflow early (E wave) and atrial (A wave) filling velocity, and atrial volumes measured on 2D from the apical four-chamber and modified apical two-chamber views [23]. Global longitudinal strain will be measured by speckle-tracking analysis of 2D images acquired at end-expiration in the apical four-, two- and three-chamber views in accordance with current guidance [24].3.Cardiovascular magnetic resonance imaging

Participants will undergo CMR imaging as part of the research study or as clinically indicated. These will occur at Birmingham (UK), Barts Heart Centre, Manchester Royal Infirmary, Addenbrookes Hospital and Royal North Shore Hospital (Sydney, Australia). A 1.5-Tesla MR system (Avanto (UK), Aera (Australia), Siemens Healthcare, Erlangen, Germany) and a standard protocol including LV cines in short axis (SAX), four-chamber, two-chamber and three-chamber views (ECG R wave gated steady-state free precession imaging) will be used. Native T1-mapping will be performed before and after contrast administration by using a Modified Look-Locker Inversion (MOLLI) recovery sequence (8-mm slice with a 192 read-out matrix, 6/8 phase partial Fourier with 81% phase resolution, repetition time 2.4 ms, echo time 1.01 ms, 11 phases; 3, 3, 5 scheme). The resulting pixel-by-pixel T1 colour map will be displayed by using a customised 12-bit lookup table, where normal myocardium will be defined as purple, increasing T1 as pink/red, and decreasing T1 as dark blue. T2 colour maps will be similarly formed, and increasing T2 will be shown as orange/yellow. LGE imaging will be performed by using phase-sensitive inversion recovery (bolus administration of gadolinium based contrast 0.1 mmol/kg body weight) to quantify the location, pattern and extent of LGE. Image analysis will be performed offline by an accredited cardiologist or radiologist at each centre by using Cvi42 (Circle Cardiovascular Imaging Inc., version 5.3.4, Calgary, AB, Canada) and will include assessment of ventricular mass, volumes, tissue characterisation with T1/T2 mapping and assessment for the presence of LGE by using methodologies previously described [25].4.12-lead ECG and advanced ECG analysis

All ILRs for participants within the UK will be followed up using home monitoring (FocusOn, Medtronic and Fysiologic BV, Amsterdam, The Netherlands). This is a continuous cardiac monitoring and triage service. Data will automatically be sent to the research team within the lead study site (Birmingham), and information will be disseminated to the participating clinical sites if required. Surveillance of the Australian participants will be carried out by using remote home monitoring (Medtronic Reveal LINQ Monitoring Service, Medtronic Australia), and data transferred to Royal North Shore Hospital where it will be disseminated to relevant clinical sites if required. Monitoring information will be transferred to the central study site on the basis of suspected clinical urgency (red: urgent, within 24 h; amber: less urgent, within 48 h; green: routine, within weekly reports). Detailed classification of arrhythmia can be seen in Additional file 2.7.ILR removal

The device will be removed after 3 years of being *in situ* in accordance with centre-specific policy. The ILR device will also be removed in those reaching a study primary endpoint requiring implantation of an alternative cardiac device (PPM, ICD or CRT). These patients will continue ongoing follow-up with arrhythmia surveillance via their new device.

### Outcome measures

#### Primary endpoints

The primary endpoint of this study will include any clinically significant arrhythmia requiring initiation or modification of treatment, which includes the following:Atrial fibrillation requiring anticoagulation (defined as an episode of arrhythmia for a duration greater than 30 s) [27]Bradyarrhythmia requiring pacing (this would include any symptomatic significant AV block and Mobitz type 2 AV block or complete heart block irrespective of symptoms) [28]Supraventricular arrhythmia requiring drug treatment or ablationNon-sustained ventricular tachyarrhythmia requiring drug treatment, ICD implantation or ablation (defined as three or more ventricular beats at a rate of more than 120 beats per minute for a duration of less than 30 s) [29, 30].

#### Secondary outcome measures

Secondary outcome measures will be evaluated providing detailed information on arrhythmia in FD. These include the following:Quantification of the arrhythmic burden in FD in those with or without LGECharacterise the relationship between arrhythmia burden and advanced CMR tissue characterisation techniques (T1 and T2 mapping)Assess the value of ECG abnormalities, particularly a QRS duration greater than 120 ms, in predicting arrhythmiaAssess the predictive value of advanced ECG analysis in arrhythmiaEvaluate the role of atrial size in burden of AFDetermine the effect of LVH and LV mass on arrhythmia burdenAssess the relationship of MSSI (a severity score index used in FD) and burden of arrhythmiaEvaluate the effect of variations in blood biomarkers (high-sensitivity troponin, lyso-Gb3, hs-CRP and IL-6) on the development of arrhythmia.

All endpoints will be reviewed and verified by a data monitoring committee.

### Statistical analysis

#### Sample size calculation

There is a paucity of knowledge about the burden of arrhythmia in FD; based on the available literature and our own collective experience, the following conclusion can be made about the necessary sample size for this study.

Existing literature has shown that over a 7-year period the incidence of arrhythmia in FD patients under standard follow-up at a specialist centre (with annual ECG recording and symptom driven investigation) is: atrial fibrillation 6%, bradyarrhythmia requiring device implantation 6% and cardiac event-related death 3% [30]. These were evenly spread over the 7-year study period with increased rates in the older age group. Assuming an even spread of events detectable over the 3 years of our study, we estimate the background detection rate of clinically significant events in those meeting the inclusion criteria and following standard care to be 5%.

In an enriched population with advanced cardiac involvement identified by the presence of LGE and LVH, undergoing routine annual 24-h Holter monitoring, the rate of identification of significant arrhythmia and sudden cardiac death was 24.6% [31]. Despite assuming a lower event rate in patients meeting the inclusion criteria for this study, we estimate the detection rate in the study group with ILRs will be 20% due to more accurate identification of all arrhythmia by these devices. With these values, for a given population proportion of 0.05 versus 0.2, sample sizes 82 and 82 in the intervention and control study arms, respectively, and an alpha of 0.05 (two-tailed), the power of the study is 80%. This means that 80% of studies would be expected to yield a significant effect, rejecting the null hypothesis that the two populations have identical event rates requiring intervention.

#### Planned statistical analysis

Statistical analyses will be carried out by using SPSS 23 (IBM Corporation, Armonk, NY). All continuous variables will be expressed as mean ± standard deviation, and all non-continuous data will be expressed as frequencies or percentages. Normality will be evaluated by using the Shapiro–Wilk test. The independent *t* test will be used to compare parametric data, and the Mann–Whitney *U* test will be used for non-parametric data. Chi-squared or Fisher’s exact tests will be used to compare proportions within two independent groups. For comparisons of repeated sample results, repeated measure analysis of variance (ANOVA) with post-hoc Bonferroni correction will be used. Time-to-event (survival) analysis will be performed to evaluate the presence of arrhythmic events during follow-up. Kaplan–Meier curves will be used to estimate the cumulative probability of arrhythmic events, and Cox proportional hazards regression will be used to evaluate the relationship between predefined covariates and outcome events. A *P* value of less than 0.05 will used for statistical significance.

All patients will have a minimum of 18 months’ follow-up for the primary outcome before interim safety analysis, which will be performed on an intention-to-treat basis. The relationship between arrhythmic burden and all other variables will be analysed by using the methods described above. An alpha spending function method will be used for the interim analysis, and a critical *P* value of less than 0.01 will be used to signify statistical significance.

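### If Fig. 2 blocks randomisation within five risk-factor groups, a test stratified by those groups is a free, mostly small gain over the unstratified chi-squared or Fisher test named

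*Protocol article*

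**What the plan says.** The Randomisation section states: "A block randomisation process will be performed by an independent statistician in a 1:1 ratio (Fig. 2". The caption of that figure, which is titled as the block randomisation process, sets target numbers by count of high-risk features: "zero risk factors – 20 participants, one risk factor – 40 participants, two risk factors – 40 participants, three risk factors – 40 participants", and "four or five risk factors – 24 participants". These add up to 20 + 40 + 40 + 40 + 24 = 164, the planned minimum. The caption gives the purpose as follows: "There will be a variable number of patients from each high-risk feature group to ensure a variable risk profile within the study cohort". Of the same features, the Participants section says: "The following features have been linked to an increase in the risk of cardiac arrhythmia and SCD".

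The Sample size calculation compares 5% with 20% at 82 per arm, two-sided alpha 0.05, and states 80% power. The Planned statistical analysis section lists tests by type of data. For proportions it gives chi-squared or Fisher's "exact tests will be used to compare proportions within two independent groups". For arrhythmic events it adds Kaplan-Meier curves, and "Cox proportional hazards regression will be used to evaluate the relationship between predefined covariates and outcome events". It mentions no stratified comparison of the arms.

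**The concern.** Balancing the arms on groups that predict the outcome removes part of the chance difference between them. A test that treats the arms as two simple independent samples still counts that part in its variance. Its true type I error then falls below the nominal 5%, and it loses some power.

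The article calls the grouping features risk factors for arrhythmia, yet the test of proportions that it names ignores the groups. What is at stake is efficiency, in a rare disease where further recruitment is hard. A false positive result does not become more likely.

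**Working it through.** **Inputs from the article.** 82 per arm; 5% v 20%; two-sided alpha 0.05; groups of 20/40/40/40/24, hence 10/20/20/20/12 per arm if blocks run within groups.

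**Assumed.** The event rates per group, which the article does not give. Overall rates are held at about 5% and 20%.

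**Step 1: the stated power.** Exact enumeration at 82 per arm gives 80.5% for Fisher and 85.8% for Pearson chi-squared; the pooled normal formula gives 83.4%. The stated 80% therefore matches unstratified Fisher.

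**Step 2: why ignoring the groups is conservative.** With group weights w and rates p, the variance that remains after balancing, relative to the variance the unstratified test uses, is

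r = Σ w p(1 − p) / [p̄(1 − p̄)].

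The true type I error is then about 2[1 − Φ(1.96/√r)]. At an overall rate of 12.5% in both arms:
- 5-fold risk gradient: r = 0.976, 1.96/√0.976 = 1.98, error about 4.7% (simulated 4.6%).
- 18-fold risk gradient: r = 0.906, 1.96/√0.906 = 2.06, error about 3.9% (simulated 3.9%).

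**Step 3: how steep could the gradient be?** The article cites 24.6% on annual Holter in patients with LGE and LVH. That figure includes sudden death, and its follow-up time is not given. If only the top group had this rate under standard care, an overall 5% would leave (0.05 × 164 − 0.246 × 24)/140 = (8.2 − 5.9)/140 = 1.6% in everyone else. This is an extreme case, not an estimate.

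**Step 4: simulation** (200,000 trials per row). With m participants per arm and k events in a group, the CMH statistic without continuity correction is

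z = |Σ(events in ILR arm − k/2)| / √Σ[k(2m − k)/(4(2m − 1))].

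The 5- and 18-fold rows use a constant risk ratio; the 12-fold and top-group rows use a constant odds ratio.

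| Assumed control-arm rates | Power %: Fisher / chi-squared / CMH | Type I error % at 12.5% in both arms: Fisher / chi-squared / CMH |
|---|---|---|
| Flat, 5% | 80.6 / 85.9 / 86.0 | 2.9 / 4.8 / 4.9 |
| 1.6% to 8.2% (5-fold) | 80.5 / 86.0 / 86.4 | 2.8 / 4.6 / 4.9 |
| 1% to 12% (12-fold) | 80.9 / 86.3 / 87.3 | 2.6 / 4.2 / 4.9 |
| 0.7% to 13% (18-fold) | 81.9 / 87.2 / 89.1 | 2.3 / 3.9 / 4.9 |
| Top group 24.6%, rest 1.6% | 83.4 / 88.7 / 93.1 | 1.2 / 2.3 / 4.9 |

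A separate run with 10- to 20-fold gradients in odds gave type I error of 2.4-2.7% (Fisher), 4.0-4.4% (chi-squared) and 4.8-4.9% (CMH). Power was about 81-82%, 86-87% and 87-88%.

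**Step 5: separate the two sources of gain.** From chi-squared to CMH, which is the effect of stratifying, the gain is 0.1, 0.4, 1.0, 1.9 and 4.4 points down the table. From Fisher to chi-squared, which is discreteness, it is 5.3, 5.5, 5.4, 5.3 and 5.3 points. Discreteness thus supplies most of the gap between Fisher and CMH except in the last row, where it is still more than half (5.3 of 9.7).

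**Step 6: the continuity correction.** Corrected CMH has power 78.8% (flat), 79.6% (5-fold), 81.0% (12-fold) and 83.2% (18-fold). That is below Fisher in the first two cases and about equal in the third, so the correction removes most of the benefit.

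**The case against.** The strongest objection is that the article fixes neither premise. The line on chi-squared and Fisher tests is one entry in a general list and is not tied to the primary endpoint. The same section plans time-to-event analysis and Cox regression with predefined covariates. The text never calls the randomisation stratified, the figure itself is not available, and the caption could describe cohort composition only. Stratification factors and covariate adjustment are often left to a full protocol or SAP, and neither is shown.

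Much of this stands. That the unstratified test is primary, and that blocks run within groups, are both inferences. They are reasonable ones: the Randomisation section cites Fig. 2 for the 1:1 blocks, the group targets add up to exactly 164, and the power calculation is for two simple proportions and matches Fisher. The comment is therefore on a method the article names, but it must be conditional.

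A reader might infer more, and three stronger readings fail:
- **The trial is underpowered or wastes much power.** Unstratified Fisher kept at least 80% in every scenario, and stratifying alone adds 0-2 points unless risk is very concentrated.
- **The groups are known to have very different event rates.** The article says only that the features are linked to higher risk, and it concedes that little is known about arrhythmia burden.
- **Holter type is a further ignored source of variation in the control arm.** The Design section does allow "standard of care using annual 24-h/5-day ECG monitoring according to local practice". But the 12-lead ECG section gives annual Holter to all participants, including the ILR arm, and the effect has not been quantified.

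**Conclusion.** The point holds as a conditional efficiency improvement. If randomisation is blocked within the Fig. 2 groups, an unstratified test is conservative to a degree that depends on an unknown gradient. Under assumed 10- to 20-fold gradients, chi-squared runs at about 4.0-4.4% and Fisher at 2.4-2.7%, while CMH stays near 4.9%. Fisher is already at about 3% with no gradient at all.

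The power gain from stratifying is 0-2 points over chi-squared for flat to moderate gradients and 4-5 if risk sits mainly in the top group. Over Fisher it is about 6 points, mostly from avoiding discreteness. The stated 80% reproduces and the type I error limit is not breached, so neither the sample size nor the validity of the test is in question. All sizes rest on exact 1:1 balance within groups and on assumed group rates.

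**What to change.** 1. State whether randomisation is stratified by the Fig. 2 groups.
2. If it is, name as the primary analysis the proportion with a primary event by 36 months, intention to treat, compared by a CMH test stratified by those groups without continuity correction. Report a Mantel-Haenszel risk difference with 95% CI. Check that the software output used is the uncorrected statistic.
3. Stratify the between-arm log-rank and Cox analyses by the same groups.
4. Define the top stratum as four or more features. Fig. 2 lists six features (LVH, LA dilatation, troponin, QRS duration, LGE, MSSI), but its last group stops at five, so a participant with all six has no stratum.
5. Adjustment for Holter type is optional, as a sensitivity analysis only.

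The cost is analysis wording, set before data are compared by arm. No further participants or data are needed, and the sample size can stay as it is.
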